## Abstract

Psychosocial factors play an important role in non-communicable diseases (NCDs). This observational study is primarily aimed at assessing the relationship of psychological characteristics of patients with the outcomes of different NCDs, and to assess short-term psychotherapy (STP) efficacy in the real world. **Methods**: One hundred and forty patients with recent acute myocardial infarction, Takotsubo syndrome, or non-metastatic breast cancer and a control group of 140 age and sex-matched healthy subjects, will be enrolled. All subjects will be administered psychometric tests, quality of life tests, a specific body perception questionnaire, a dream questionnaire, and a projective test, the Six Drawing test at baseline and follow-up. All subjects with medical conditions will be asked to freely choose between an ontopsychological STP along with standard medical therapy and, whenever indicated, rehabilitation therapy or medical therapy plus rehabilitation alone. The study endpoints will be to evaluate: the relationship of the psychological characteristics of enrolled subjects with the outcomes of different NCDs, predictors of the choice of psychotherapy, and the efficacy of ontopsychological intervention on psychological and medical outcomes. **Conclusion**: This study will generate data on distinctive psychological characteristics of patients suffering from different CDs and their relationship with medical outcomes, as well as explore the efficacy of ontopsychological STP in these patients in the real world. (Number of registration: NCT03437642).

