#### 3.2.2. Treatment Choice, Implementation, and Group Allocation

In the second phase, all pts with TTS, AMI, and BC will be asked to freely choose between ontopsychological STP along with standard medical therapy and, whenever indicated, rehabilitation therapy or medical therapy plus rehabilitation alone.

Therefore, this phase results in seven study groups: three groups of pts (AMI, TTS, and BC) undergoing psychotherapy, three groups of pts (AMI, TTS, and BC) on standard medical therapy, and one group of HS.

There will be four independent areas of research: (1) AMI pts following psychotherapy (AMI-PSY) will be compared with AMI pts, without psychotherapy (AMI-C); (2) TTS pts who will follow psychotherapy (TTS-PSY) will be compared with TTS pts without psychotherapy (TTS-C); (3) BC pts with psychotherapy (BC-PSY), will be compared with BC pts without psychotherapy (BC-C); (4) HS subjects, after the initial comparative evaluation with the other enrolled groups, will have an independent follow-up, where psychological data collected at enrollment will be compared with psychological data collected at one year and with clinical follow-up at five years.

Since the research is observational, it is not possible to foretell how many patients will choose psychotherapy plus medical therapy or standard medical care alone.

If balanced patient groups can be formed, statistical analysis evaluating differences between groups will be performed. Thus, it may be possible to evaluate how psychotherapy may impact the real world because patients will have a choice between psychotherapy plus medical care or medical care alone. It will also be possible to evaluate if psychotherapy might result in an improvement in psychological patterns compared to medical therapy alone, and how this can translate in an improvement in medical prognosis. Moreover, the patients’ choice might provide useful information to improve a more individualized therapy and hospital organization.

AMI-PSY and TTS-PSY patients will be referred to the outpatient clinic of Cardiac Psychology at San Filippo Neri Hospital in Rome; BC-PSY will be referred to the outpatient clinic of Psycho Oncology in the same hospital. Psychotherapy will be provided in individual sessions (maximum of ten) and five group meetings, as in the STEP IN AMI trial. Psychotherapy will be conducted by two expert psychotherapists trained in ontopsychology and psychosomatics.

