## 4. Statistical Analysis

An external committee will evaluate the results in each phase of the research and the characteristics of each group will be analyzed. The qualitative results related to the 6DT, body perception questionnaire, and dream questionnaire at enrollment and the one-year follow-up. It is impossible to foretell the specific features of oneiric symbols and patterns before the study, as the research is a pilot study in the field of psychosomatics. The oneiric manual of the ontopsychological school [45] will be used as an initial reference point for the analysis and classification of dreams.

Unless otherwise specified, all study data will be analyzed on an intention-to-treat basis.

Event rates will be expressed as proportional incidences and as person−time incidence rates. Continuous variables for each of the study groups will be reported as means (with standard deviations or 95% confidence intervals) or as medians (lower quartile-upper quartile), as appropriate; categorical variables will be reported as absolute numbers and percentages. Continuous unpaired variables will be compared using the independent-sample Student’s t or Mann-Whitney U tests, and continuous paired variables will be compared using paired Student’s t or Wilcoxon tests, as appropriate. Categorical variables will be compared by Pearson’s chi-squared analysis or Fisher’s exact test, as indicated. The outcome incidence within each study group over long-term follow-up will be compared with Friedman’s test. Survival analysis will be performed using Cox proportional hazards ratios. Multivariable binary logistic regression analysis will be performed to appraise the independent predictive role of baseline characteristics on outcomes. Spearman’s rank correlation test will be performed to assess the correlation between variables. A *p* value < 0.05 will be considered statistically significant, with all inferential tests 2-tailed. Statistical analysis will be performed using the statistical software program SPSS, version 11.5 (SPSS Inc., Chicago, IL, USA).

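### Patients choose psychotherapy themselves, but no adjusted analysis is named for the therapy contrast, so a crude comparison would mix the therapy effect with who chooses therapy

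*Protocol article*

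**What the plan says.** Section 3.2.2 forms the treatment groups by preference: "all pts with TTS, AMI, and BC will be asked to freely choose between ontopsychological STP along with standard medical therapy", or standard care without psychotherapy. It then sets up a separate comparison of choosers and decliners within each of the three diagnoses.

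The Abstract lists among the endpoints "the efficacy of ontopsychological intervention on psychological and medical outcomes", and also "predictors of the choice of psychotherapy". Section 3.2.2 adds: "It will also be possible to evaluate if psychotherapy might result in an improvement in psychological patterns compared to medical therapy alone", and goes on to how this might carry over to medical prognosis.

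Two conditions precede the comparison. Section 3.2.2 requires that balanced groups can be formed, without defining balance. Section 3 (B) makes the medical endpoints depend on whether the chooser and decliner groups are large enough.

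For analysis, section 4 gives t or Mann-Whitney tests for continuous variables and, for the rest, "Categorical variables will be compared by Pearson’s chi-squared analysis or Fisher’s exact test, as indicated". Cox regression is listed with no covariates named. The only multivariable model is introduced by this sentence: "Multivariable binary logistic regression analysis will be performed to appraise the independent predictive role of baseline characteristics on outcomes".

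**The concern.** When patients pick their own treatment, whatever drives the choice may also drive the outcome: age, severity of disease, baseline distress, social support, education, motivation. The authors treat the choice as something patient characteristics may predict, since its predictors are an endpoint. Yet nothing in the article carries those predictors into the therapy comparison.

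The interpretation of the efficacy endpoint is at stake. A crude difference between choosers and decliners cannot be read as an effect of psychotherapy, and its p value reflects sampling error only, not the selection. With groups of 55, 55 and 30 patients, each split further by choice, a sizeable baseline imbalance would be unsurprising.

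**Working it through.** **Step 1. The plan's own figure.** Inputs from Sample Sizing and section 4: 43% versus 78% events at one year, 80% power, two-sided 0.05. An equal split is my assumption, because the plan fixes none. With unpooled variance:

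n per group = (z₀.₉₇₅ + z₀.₈₀)² × [p₁(1−p₁) + p₂(1−p₂)] / (p₂−p₁)²

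= 7.849 × (0.2451 + 0.1716) / 0.35² = 26.7, so 27 per group and 54 in total. This is close to the stated 55. (Pooled variance gives 30 per group, 60 in total.) The 55 is thus consistent with a plain two-proportion comparison at rates from a randomised trial, with no allowance for self-selection.

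**Step 2. Does anything in the text protect the therapy contrast?**

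| Element | Where | Effect on confounding by choice |
|---|---|---|
| t, Mann-Whitney, chi-squared, Fisher | 4 | None; unadjusted by construction |
| Cox regression | 4 | Could carry covariates; none named |
| Multivariable logistic model | 4 | Purpose is prognostic; therapy not named as the exposure |
| Intention-to-treat | 4 | Without randomisation, keeps the chosen groups and their selection |
| Balanced groups | 3.2.2 | Undefined; may mean size only |
| Sufficient group size | 3 (B) | Equal or large groups can still differ at baseline |

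**Step 3. How large could the bias be?** The documents give no inputs, so these are assumptions. Suppose therapy has no effect and one binary factor changes event risk. Then:

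spurious risk difference = (difference in prevalence of the factor between decliners and choosers) × (difference in event risk due to the factor)

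- Low end: 0.20 × 0.20 = 0.04, or 4 points.
- High end: 0.40 × 0.40 = 0.16, or 16 points.

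An example of the high end: event risk is 85% with the factor and 45% without, and 30% of choosers and 70% of decliners carry it.

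- Choosers: 0.30 × 0.85 + 0.70 × 0.45 = 0.57
- Decliners: 0.70 × 0.85 + 0.30 × 0.45 = 0.73

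With 27 and 28 patients, an unadjusted two-sided 5% test of 57% versus 73% favours therapy with probability about 0.235, although therapy does nothing. The nominal figure in that direction is 0.025. At the low end (63% versus 67%) the probability is about 0.05. Reversing the prevalences reverses the bias, so that it would hide a real benefit.

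**Step 4. How much adjustment can the data carry?** Take the infarction group at an equal split and the planning rates. Events: 27.5 × 0.43 + 27.5 × 0.78 = 33.3. Non-events: 55 − 33.3 = 21.7. At 10 per parameter (a rule of thumb), a logistic model holds about 21.7 / 10 ≈ 2 parameters, one of them therapy. In the Takotsubo group the Enrollment Status section shows 15 of 19 choosing therapy, which leaves 4 decliners so far.

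**The case against.** The best defence is that this is a condensed article. Section 4 reads as a list of methods by type of variable, assigns none of them to the therapy contrast, and includes two regression methods that could hold therapy and covariates. Covariate lists are commonly left to an analysis plan. A reader might infer that the plan commits to an unadjusted Cox model. It does not; the covariates are simply not named. What survives is narrower. The simple tests are unadjusted as written, and the one multivariable model is given a different job, so the article points away from an adjusted therapy effect.

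A reader might also infer that the plan draws an efficacy conclusion from self-selected groups. The wording is more careful: the Abstract speaks of exploring efficacy, section 3.2.2 of what might be evaluated, and the Discussion of preliminary testing and of the known limits of observational studies. The Discussion also puts the qualitative description at enrollment first. That lowers the stakes but does not remove the point, because efficacy remains a named endpoint and the infarction group is sized on this contrast.

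The comparison is conditional and may never be run. The conditions, however, govern whether it is run, not whether the groups are comparable when it is.

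Finally, the uptake so far (15 of 19 Takotsubo, 5 of 11 breast cancer, 1 of 4 infarction) invites the reading that selection is already visible. It is not evidence of that. These figures differ between diagnoses, while the contrasts are made within each diagnosis, so diagnosis cannot confound them.

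**Conclusion.** The point holds in this form: treatment is self-selected, the contrast is meant to inform efficacy, and the article names no analysis that adjusts it. Followed as written, the comparison is open to confounding by choice, and neither the balance condition nor the size condition prevents this.

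The size and direction of the bias in this study are unknown. The 4 to 16 points, and the chance of about 0.05 to 0.235 of a spurious result favouring therapy, rest wholly on the assumed risks and prevalences and on an equal split of 55 patients. They show that the bias could be material beside a planned difference of 35 points, not that it will be.

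**What to change.** Within each diagnosis, keeping the three comparisons separate because the breast cancer endpoint differs from the cardiac one:

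- Make the main chooser-versus-decliner analysis a model with therapy as the exposure, adjusted for a very short prespecified list of baseline data already collected under sections 3.1 and 3.2.1, for example age and the baseline value of the outcome score or the Beck Depression Inventory.
- For psychometric scores, use ANCOVA on the follow-up score with its baseline value as covariate.
- For medical endpoints, use Cox or logistic regression, penalised or propensity-weighted where events are few.
- Define balance in section 3.2.2 as baseline comparability as well as size.
- Keep the t, Mann-Whitney, chi-squared and Fisher comparisons as descriptive.
- Report the result as an adjusted association. Where a group is too small to adjust, as Takotsubo may be, describe the contrast without an efficacy claim.

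The cost is a change of wording and some analysis work; no new data are needed. Intervals will be wider. The infarction event model has room for therapy and about one covariate unless penalisation or weighting is used. Confounding by factors left out of so short a list, or not measured, will remain and must be stated.

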### 2.1. Aims

(1)To prospectively assess the clinical and psychological characteristics at enrollment, and the real-world outcomes at one and five years in patients (pts) with AMI, TTS, and BC who (a) have undergone ontopsychological STP or (b) declined the treatment, as well as (c) a control group of age/sex-matched subjects without major active diseases (for a practical exposition they are referred to as “Healthy Subjects”, HS) not undergoing psychotherapy at enrollment(2)To assess:
The perception of their body and emotions in each group at baseline and follow-up;Dream symbols and patterns in each group, including retrospective evaluation of past dreams (until childhood and adolescence), at baseline and follow-up;Specific psychodynamic patterns in each group based on personal history, dream analysis, psychometric tests, and the projective non-structured Six Drawing test (6DT) [27,28];The correlation of past dream symbols and patterns with the onset of disease in each group;The correlation between baseline psychological data/evaluations and study outcomes.

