##### Sample Sizing

The size of the AMI group has been based on evaluation of the outcome data at one year from the results of the STEP-IN-AMI trial: a 43% incidence of the primary composite endpoint is expected in the psychotherapy group and 78% in the control group; therefore, 55 pts will be enrolled to achieve statistical power at the 95% confidence level with 80% power. Given the exploratory nature of the study in the other groups, which renders impossible any hypothesis on the effects of psychotherapy, statistical sample sizing has not been performed in these groups. To match the AMI group, 55 women with BC will also be enrolled. However, only 30 patients with TTS will be enrolled for feasibility reasons, due to the lower percentage of patients admitted to the hospital as compared to the other study groups which could unreasonably slow the enrollment phase. Consequently, it will be necessary to enroll 140 HS in the control group.

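### Ordinary multivariable logistic regression is a weak basis for claiming independent predictors in groups of 30 to 55; a Firth model with a few prespecified terms would serve better

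*Protocol article*

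**What the plan says.** Section 4 of the protocol article (Statistical Analysis) names the method and its purpose: "Multivariable binary logistic regression analysis will be performed to appraise the independent predictive role of baseline characteristics on outcomes". The criterion for all tests is unadjusted: "A *p* value < 0.05 will be considered statistically significant, with all inferential tests 2-tailed".

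The model serves a central question. Section 2.1 (Aims) lists "The correlation between baseline psychological data/evaluations and study outcomes", and the Abstract puts the relation of psychological characteristics to outcomes first among its purposes.

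On numbers, Sample Sizing says of AMI that "55 pts will be enrolled to achieve statistical power at the 95% confidence level with 80% power", based on "a 43% incidence of the primary composite endpoint is expected in the psychotherapy group and 78% in the control group". For the other groups it says "To match the AMI group, 55 women with BC will also be enrolled" and "only 30 patients with TTS will be enrolled for feasibility reasons". No event rate is given for BC or TTS. Because treatment is chosen by the patient, "it is not possible to foretell how many patients will choose psychotherapy".

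Section 3.1 (Tests) lists the baseline battery. Section 3 (Endpoints and Outcome Measures) gives AMI and TTS one shared medical composite, gives BC a different one, and adds new hospital admissions for all patients.

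**The concern.** A multivariable model is the only listed analysis that is said to show an independent role for baseline traits. Ordinary maximum likelihood logistic regression is biased away from zero in small samples, and it fails under separation, when the covariates split events from non-events perfectly. How badly depends on the smaller of the event and non-event counts relative to the number of coefficients. The sample size was set for a two-group comparison of proportions in AMI, not for this model, and the battery is long compared with what the groups can carry.

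The Discussion says the findings should generate working hypotheses to better target interventions. Inflated odds ratios, or chance findings called independent predictors, would be carried into that work.

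**Working it through.** **The plan's own figure.** Take the two-proportion formula with unpooled variance, two-sided 0.05, 80% power and an even split:

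n per arm = (1.960 + 0.842)² × (0.43×0.57 + 0.78×0.22) / (0.78 − 0.43)² = 7.85 × 0.4167 / 0.1225 = 26.7, so 27 per arm and 54 in total.

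This agrees with 55 and shows what 55 was sized for. The article gives no figure for the regression.

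**Scores available (section 3.1).**
- AMI and TTS: Self-evaluation test 1, Social Support Questionnaire 1, BDI 1, STAI 2 (state, trait), STAXI 2 at least 1, MacNew 4 (three domains and global). Total at least 10.
- BC: the same first 6 plus 9 QLQ-C30 scales. Total at least 15, before QLQ-BR23.
- Body perception, dream, Six Drawing and clinical variables come on top.

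**Coefficients supported.** The convention used here (an assumption, not in the article) is ten of the rarer outcome per coefficient.
- AMI, even split: overall rate (0.43 + 0.78)/2 = 0.605. Events 55 × 0.605 = 33.3 and non-events 21.7, so 21.7/10 = about 2.
- TTS alone, borrowing that rate: 30 × 0.395 = 11.9, so about 1. At an assumed 20% rate: 6 events, so fewer than 1.
- AMI plus TTS on the shared composite, same rate: 85 × 0.395 = 33.6, so about 3.
- All 140 on admissions: 28 events at an assumed 20%, so about 3; 140 × 0.395 = 55.3 at 60.5%, so about 5.

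**If ten pure-noise scores were entered.** Simulation used 1,500 data sets per setting, event rates of 43%, 60.5% and 78% from the article plus an assumed 20%, and correlation between scores of 0 or 0.5.

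| n | at least one Wald p<0.05 | separation |
|---|---|---|
| 55 | 37-46% | 1.8% at 20% events, correlation 0.5 |
| 30 | 4-25% | 7-49% |

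At n=55 the median odds ratio of the significant noise predictors was 2.6-5.7 per SD. At n=30 the Wald test flags fewer predictors because near-separation inflates the standard errors. Those it does flag had median odds ratios of about 7 to 23 per SD.

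**If few terms were entered.** At a 60.5% event rate and correlation 0.5, three noise predictors at n=55 gave a false finding in 12.5% of models, and two at n=30 in 6.6%.

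**Bias with only four predictors.** With a true log odds ratio of 0.6 (odds ratio 1.82), maximum likelihood inflated the mean estimate by about 14% at n=55 and 38% at n=30; Firth by about 0% and 4%. On the odds ratio scale, 0.6 × 1.14 = 0.684 gives 1.98, and 0.6 × 1.38 = 0.828 gives 2.29.

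A check had one real and three null predictors, event rates of 60.5% and 40%, correlations 0 to 0.5 and 3,000 data sets per setting. Maximum likelihood gave 15-19% and 33-40%; Firth gave 1-4% and 1-6%. The estimates are skewed: median maximum likelihood inflation was 10-13% at n=55 (0.662-0.679 against 0.6) and 20-24% at n=30 (0.717-0.744).

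**The case against.** A reader might infer that the plan puts ten or more scores into one model. It does not say so. The covariate list is commonly left to an analysis plan, and two or three prespecified predictors would fit the sentence as written. The absence of a list is therefore no fault in itself, and the ten-score figures are conditional.

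A reader might also infer separate models in each disease. Section 3.2.2 calls the groups independent areas of research, but that describes the psychotherapy comparisons and the follow-up of healthy subjects. The shared composite allows 85 cardiac patients in one model, and admissions allow 140. The separation figures apply only if TTS is modelled alone.

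Two stronger claims should not be made. One is that false predictors are bound to appear: even with ten scores at n=55, more than half of the noise models show none. The other is that logistic regression is unusable whatever covariates are chosen: with about two terms it is workable. No measure of discrimination is planned, so none is criticised here.

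The false-positive rate is also mainly multiplicity. Ten independent tests at 0.05 give 1 − 0.95¹⁰ = 40.1%, and ten scores in all 140 patients still give about 41%. Penalisation is not the remedy for that; limiting the terms is.

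Finally, the article calls the work exploratory and a pilot, and the Discussion describes its primary design as a qualitative analysis at enrollment. That moderates what is at stake, but it does not correct an inflated odds ratio. The bias at four predictors also needs no assumption that the whole battery is entered.

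**Conclusion.** The concern holds in a limited form. The article fixes an unpenalised model for a claim of independence in groups that support about two coefficients (AMI) or about one or fewer (TTS alone). With a modest four-predictor model, mean log odds ratios would be too large by about 14% at n=55 and 38% at n=30, and Firth estimation largely removes this. If about ten scores were entered, a noise predictor would reach p<0.05 in roughly 37-46% of models at n=55, and a TTS-only model would separate in about 7-49%.

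These sizes rest on an even split of treatment choice, no dropout, equal correlations between scores, and assumed event rates for TTS and BC, for which the article gives none. An uneven split would change the AMI counts. The point is an improvement to the stated method, not evidence that the planned analysis must fail.

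**What to change.** In section 4, replace the ordinary model by Firth-penalised logistic regression with a small number of psychological terms chosen before outcomes are seen, about two per disease model and one score per construct. Any term for psychotherapy or a clinical factor counts against the same budget.

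Use the shared composite to model AMI and TTS together (85 patients, stratified by disease), and all 140 patients, again stratified, for hospital admissions. Report every other score as a univariable estimate with its interval, labelled exploratory and not called an independent predictor.

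The cost is a change of wording. Fewer traits can be called independent predictors, and software that fits Firth models may be needed beyond the named SPSS 11.5. At the time of the article 19 + 11 + 4 = 34 of 140 patients were enrolled, so the terms could still be fixed before most outcomes were known.
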